## Abstract

**Introduction::**

Chronic renal disease (CRD) affects a large portion of the population and is directly related to cardiovascular problems and hypertension, among others. Studies show that heart rate variability is directly affected by these problems. Physical-oriented exercises have been shown to be of fundamental importance in improving the adverse effects to dialysis treatment.

**Objective::**

To analyze the effects of aerobic training during hemodialysis on autonomic heart rate modulation in patients with CRD.

**Method::**

Experimental study of an open, single group clinical trial. In this clinical trial, patients with CRD will initially undergo international physical activity questionnaire and kidney disease quality of life short form protocols, as well as monitoring of heart rate systolic, and diastolic blood pressure. After evaluation of the initial parameters, patients will undergo an aerobic exercise program for 12 weeks, in 3 weekly sessions, lasting 30 minutes a session. These evaluations will allow for a greater control of the disease, and monitoring of any improvements in the quality of life and self-esteem of these patients.

**Ethics and dissemination::**

This study was approved following the guidelines and norms that regulate research involving human subjects, in Resolution No. 466/12 of the National Health Council. It was approved by the Research Ethics Committee of the Faculty of Juazeiro do Norte, with the number 1962 092. All patients who agree to participate in the research will sign the informed consent form. The results will be disseminated through peer-reviewed journal articles and conferences.

## Introduction

1

The World Health Organization (WHO) reports millions of deaths each year from chronic diseases. Among these chronic diseases, chronic renal disease (CRD) is considered a worldwide public health problem due to the high mortality rates.^[1]^ CRD has received increasing attention from the international scientific community, as its high prevalence has been demonstrated in recent studies. In Brazil, comprehensive epidemiologic studies on CRD using the new definition of the disease have not yet been performed.^[2]^ While the number of Brazilians in the different predialysis stages of CKD (Chronic renal kidney) is not known accurately, an analysis of adult laboratory data using the new definition of CKD revealed that 2.3% of subjects had glomerular filtration rate (GFR) <45 mL/min/1.73 m^2^ or chronic renal disease (CRD) stages 3B, 4, and 5. Extrapolating these results to the Brazilian adult population, it is suggested that about 2.9 million Brazilians would have a 3rd or less of the GFR of normal individuals.

The CRD is the slow, progressive, and irreversible loss of renal function causing the body to no longer be able to maintain metabolic and hydroelectrolyte balance.^[3,4]^ It causes serious consequences for the patient and his/her family, compromising physical, psychic, and social health, and will eventually directly affect their quality of life (QoL).^[3,4]^

Patients with CRD have shown an increase in survival due to the use of renal replacement therapy. The renal therapy of choice is a successful renal transplant, but hemodialysis and peritoneal dialysis present similar clinical results, and so are the most commonly used treatment.^[3,4]^ Patients with CRD are using hemodialysis and dialysis therapies, and they are likely to have sequelae in all areas of their life.^[3,4]^

The population of patients with CRD on hemodialysis is associated with several factors, such as: high morbidity rate, mortality, low cardiopulmonary capacity, low functional capacity, cardiovascular diseases, and arterial hypertension.^[5,6]^ Patients on chronic hemodialysis with cardiovascular disease frequently die suddenly, resulting in a high mortality rate. Heart rate variability (HRV), which describes oscillations in the intervals between consecutive heart beats (RR intervals), is influenced by the activity of the autonomic nervous system (ANS) on the sinus node. Reductions in HRV are prognostic of an increased risk of death in several populations, but its prognostic value in patients undergoing hemodialysis remains unclear.^[7]^ In addition, there is a very close relationship between CRD and systemic arterial hypertension, which could affect the cardiovascular system, and result in the dysfunction of autonomic cardiac modulation, with predominant sympathetic autonomic modulation. ANS dysfunction is commonly present in patients with CRD and patients undergoing hemodialysis, and is an independent factor for a poor prognosis and sudden death in this population.^[7,8]^ Cardiac autonomic dysregulation, shown by a reduced HRV, contributes to the high mortality observed in patients with CRD undergoing hemodialysis.^[9]^

The HRV is a noninvasive technique whose analysis can be performed using linear time and frequency and nonlinear methods in the chaos domain.^[10]^ Time domain methods use mathematically simple techniques to measure the variability present in the RR intervals by calculating the mean and standard deviation of heart rate variations over time, while frequency domain methods use the spectral analysis that monitors the decomposition of heart rate variation at a given time in its fundamental oscillatory components, that is, the time series is decomposed into different frequency components.^[10,11]^ Among the methods used for HRV analysis are the geometric methods, triangular index, triangular interpolation of the RR intervals (TINN), and Poincaré plot, which present the RR intervals in geometric patterns and use approximations to derive the measures of HRV.^[10,11]^

Knowledge of the physiologic responses involved in the exposure of patients with CRD to hemodialysis is important for the development of future therapies to monitor, intervene, or even prevent the development of cardiovascular system disorders.^[2]^ The important reduction in the functional capacity of patients with CRD treated with hemodialysis has been partially reversed with regular aerobic physical exercises.^[12]^ In addition, it may also contribute to the reduction of osteomyoarticular problems, improvement of the QoL, and improved adherence to the treatment plan.^[13]^ The National Kidney Foundation recommends that regular physical activity be part of the strategic management of patients with CRD.^[14]^

Physical training in normal individuals results in an increase in functional capacity, reduces the risk of cardiovascular diseases, and improves the psychologic structure.^[14]^ A similar benefit has been reported with dialysis patients, even though the actual impact is impaired by the difficulty of adherence to any exercise program, both in diseased and healthy individuals.^[15,16]^ Several studies have reported the effects of aerobic training in dialysis patients. The type and duration of the training programs are variable (8 weeks to 6 months), but all studies compared the patients before and after the training program.^[15,16]^

Patients with CRD on hemodialysis generally have a poor physical and psychologic condition, but we intend to demonstrate that a program of aerobic physical exercise, when well prescribed and monitored, is safe and can generate benefits for the treatment of these patients.

In this way, the present study has as general objective to evaluate the effects of aerobic training during hemodialysis on autonomic heart rate modulation and quality of life in patients with CRD, and objective specifics are as follows:

1.Describe the linear and nonlinear indexes of HRV in patients with CRD on hemodialysis during supervised aerobic exercise in cycloergometry.2.To evaluate the quality of life in patients with CRD on hemodialysis during supervised aerobic exercise in cycloergometry.

## Methods

2

This study protocol will follow the items of the Standard Protocol for Randomized Trials (SPIRIT). This is an open, single-group experimental study on the autonomic heart rate modulation response under the effects of aerobic training during hemodialysis sessions in patients with CRD.

### Study population

2.1

Patients with CRD, who are on hemodialysis, at the Hospital das Clinicas in Rio Branco, Acre State, Brazil, will be included if they meet the inclusion/exclusion criteria described in the following section.

### Inclusion and exclusion criteria

2.2

Adult patients of both sexes who have not been physically active for at least 6 months will be included. The patients have been under treatment for at least 6 months and have been clinically authorized by the physician responsible for the sector to be included in a physically active study.

Patients with diabetes mellitus, unstable angina, uncontrolled arterial hypertension (systolic blood pressure [BP]: 200 mm Hg and/or diastolic BP: 100 mm Hg), use antiarrhythmic drugs, severe pneumopathies, acute systemic infection, renal osteodystrophy, and severe, disabling neurologic, and musculoskeletal disorders will be excluded from the study.

### Expected risks

2.3

The risks are minimal, but patients may feel constrained by the exercise sessions proposed in this work and so may not wish to participate in the research. Patients may also experience dizziness, nausea, cramps, fatigue beyond the supported, and headaches. In cases of clinical problems, activities will be discontinued.

### Expected benefits

2.4

Relevant scientific information will be obtained on the recovery and rehabilitation of patients with CRD through the analysis of HRV after aerobic exercises using the cycloergometer. This will demonstrate that well-controlled aerobic physical activity can contribute to a better QoL and the psychosocial well-being of these patients, thus helping to prolong their life.

### Intervention

2.5

Liao et al^[17]^ used 2 groups of 20 patients each, performing a 30-minute exercise program consisting of a 5-minute warm-up, 20-minute electric bicycle, and a 5-minute cooling down regimen during treatment with hemodialysis in the renal unit. The exercise was performed under the supervision of a physician and a rehabilitation nurse. This was adapted in this study to be conducted in a single screening group. We also modified the procedure since the exercise will be performed on a mechanical cycle ergometer, facilitating the individualized development for each patient. The work will be overseen by a leading researcher/professional physical educator, following specific medical assessment of the site's nephrology sector.

Marques et al^[18]^ used the Borg perceived effort scale in his program to measure exercise intensity. In our case, the patients will perform aerobic exercise consisting of cyclic movements of the lower limbs. The load will be prescribed by taking into account the Karvonen scale. In Raimundo et al,^[19]^ the subjects were walked on a treadmill for aerobic exercises divided into 5 minutes of warm-up and 25 minutes of exercise, reaching 50% to 70% of their maximal HR (HR_max_). This protocol was modified so that the patients perform the aerobic exercise of cyclical movements of the lower limbs with 45% to 60% intensity of their HR_max_. The total time will be 30 minutes. They will be instructed to remain with arms extended normally in the extension of the chair next to the body, to be accommodated in the best possible way during hemodialysis. The lower limbs will perform the most active part of the exercise by executing a constant rotation of the pedals throughout the aerobic exercise in the mechanical cycler. Patients will be encouraged to increase their intensity according to individual capacity, respecting the principle of biologic individuality. Thus, our protocol consists of developing aerobic exercise 3 times a week, lasting 30 minutes for 3 months, with aerobic intensity, varying from 45% to 60% HR_max_, totaling 36 sessions.

### Instruments and data collection

2.6

The HRV assessment instrument will be applied at the beginning and end of the aerobic exercise protocol. Initially, the sample size will be 40 adult patients with CRD who undergo hemodialysis in a study with a single screening group. The present study aims to evaluate the effects of supervised aerobic exercise in cycloergometry performed in patients with CRD during hemodialysis sessions, using HRV analysis.

The kidney disease quality of life short form (KDQOL-SF)^[20]^ will specifically evaluate the QoL of the patients with CRD at the Hospital das Clínicas do Rio Branco-Acre. The international physical activity questionnaire (IPAQ) will be used to identify the level of physical activity that the patients are currently experiencing.^[21]^ In addition, information will be collected regarding the laboratory parameters of the patient's charts, and these data will be collected from the month referring to the application of the experimental protocol (Fig. 1).

**Figure 1 F1:**
[figure not shown]
Protocol stages flow chart. HR = heart rate, HR_max_ = maximum heart rate, HRV = heart rate variability, IPAQ = international physical activity questionnaire, KDQOL-SF = kidney disease quality of life short form.

Regarding the application and evaluation of the exercise, there will be 2 evaluations: The 1st is when the HRV will be determined; the 2nd evaluation will be the development of the exercises during the hemodialysis sessions (Fig. 1).

The 1st evaluation, which consists of capturing the HRV of the exercising patients, will be performed in the first 2 hours of hemodialysis, with a total duration of 1 hour. A cycle ergometer will be used to perform aerobic exercise. All patients will be monitored for cardiovascular function by a portable system (Polar RS 800 CX),^[22]^ which will allow the storage of the data for later analysis of cardiac rhythm variability.

The HR monitoring for subsequent HRV analysis will be obtained by means of a heart rate monitor (RS800CX; Polar Electro Finland Oy, Kempele, Finland) validated to locate the HR for HRV analysis, and collection will be at the beginning of the clinical intervention of the aerobic exercise sessions and after 3 months (end of the intervention), as proposed in this research and shown in Figure 1.

The cardiofrequency meter will be placed over the patient's praecordial region and secured by an elastic strap to his/her back for proper fixation (Fig. 2).

**Figure 2 F2:**
[figure not shown]
Placement of the strap on the patient. Source: Prepared by the authors, 2018.^[23]^

The recorded pulses will be directed to a computer through an infrared signal emitting interface for the analysis of the ventricular function curve (VFC) by the Polar Precision Performance software. For data analysis, the VFC will be filtered at a moderate intensity for the elimination of ectopic beats and/or noises. The HRV analysis will be performed in time and frequency domain and nonlinear methods (Fig. 3).

**Figure 3 F3:**
[figure not shown]
Transfer of data. Source: Prepared by the authors, 2018.

### Protocol's Phase Study

2.7

This protocol will be done in 3 phases:

T1: Resting stage (duration of 10 minutes): At this stage, the patient will be instructed to remain as relaxed as possible on the stretcher. They will be instructed to remain with arms extended normally in the extension of the chair next to the body, accommodated in the best possible way.T2: Intervention stage (duration of 30 minutes): Patients will perform aerobic exercise consisting of cyclic movements of the lower limbs with 45% to 60% intensity of their HR_max_. They will be instructed to remain with arms extended normally in the extension of the chair next to the body, accommodated in the best way possible (Fig. 4).The lower limbs will perform a constant rotation (pedaling) throughout the aerobic exercise in the lower leg cycle ergometer. (Mini Bike Compact - E 14) from ACTE, with multifunction LCD: scan, time, ODO-RPM, distance, calories, speed, measuring (A × C × L) 49 × 41.5 × 34.5 m, to perform aerobic exercise (Fig. 5).The patients will start pedaling and will be encouraged to increase the intensity so that it reaches the established zone, and will possibly be able to exceed the upper limit, until the intervention time is over. The load was prescribed by taking into account the Karvonen scale.T3: Recovery phase (duration of 20 minutes): Patients will be advised to be as relaxed as possible in the resting phase (recovery). All the patients will be evaluated with the instrument in the initial phase of the research to collect the HRV before the protocol of aerobic exercises proposed during one hour of hemodialysis session (as it appears in the exercise program proposed above). This same evaluation will be carried out with the same characteristics after 3 months.

**Figure 4 F4:**
[figure not shown]
Maca next to the monitoring device where the patient will perform the exercises. Source: Prepared by the authors, 2018.

**Figure 5 F5:**
[figure not shown]
Mini bike compact - E 14. Source: Prepared by the authors, 2018.

All patients will be assessed at the beginning of the exercise and every 5 minutes throughout the 30 minutes of the active phase, the HR and BP will be measured by the Bellco Formula Plus dialysis machine (Formula 2000 plus Domus SW 5.8, Mirandola, Italy) (Fig. 4).

At all stages, patients’ complementary data will be collected through their charts as completed by hospital medical staff (body mass, height, weight, age, sex, BP, and HR measurements).

In the 2nd evaluation, the exercise will last 30 minutes. The patients will perform aerobic exercise consisting of cyclical movements of the lower limbs at 45% to 60% intensity of their HR_max_. They will be instructed to remain with arms extended normally in the extension of the chair next to the body, accommodated in the best way possible (Fig. 4). The lower limbs will perform a constant rotation (pedaling) throughout the aerobic exercise in the lower leg cycle ergometer. They will start pedaling and will be encouraged to increase the intensity so that it reaches the established zone, perhaps being able to exceed the upper limit, until the intervention time is over. The load was prescribed by taking into account the Karvonen scale.

All patients will be assessed at the beginning of the exercise and every 5 minutes throughout the 30 minutes of this phase their HR and BP will be measured by the Bellco Formula Plus dialysis machine (Fig. 4).

Patients will undergo 3 weekly sessions of aerobic exercise performed during the first 2 hours of the hemodialysis sessions for 12 weeks (3 months). During collection, all patients will be instructed to avoid intense and continuous conversations.

The IPAQ is recommended by the Clinical Guidelines of the Brazilian Medical Association-Federal Council of Medicine to track the sedentary lifestyle in adults^[24]^ and was proposed by the WHO. The questionnaire will serve to determine the level of physical activity in the population; consisting of sessions with questions related to the time that people spent doing physical activity in a regular week. For this purpose, the short version of the IPAQ^[21]^ will be used.

The KDQOL-SF protocol will be used to evaluate QoL. It is a self-enforcing questionnaire of 80 items divided into 19 dimensions. It includes the short-form health survey as a generic measure and is supplemented with multi-item scales, addressing the particular concerns of chronic kidney patients. The process of coding the questionnaire obeys the “Manual for use and correction of Kidney Disease and Quality of life-Short Form-KDQOL-SF 1.3,” developed by the authors.^[20]^ In general terms, a score is given for each item (or question), and is subsequently transformed into a scale from 0 to 100, in which the value 0 reflects a worse QoL and the value 100 reflects a better QoL. The internal consistency estimated by the KDQOL-SF exceeded 0.80 (range 0.61–0.90).

In addition, information will be collected regarding laboratory parameters of patients’ records, and these data will be collected from the month referring to the application of the experimental protocol.

## Results

3

### Primary outcomes

3.1

Recruitment began in November 2017 and is underway. A total of 40 patients should be evaluated and submitted to protocol intervention by the end of this study.

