### Secondary outcomes

3.2

The protocol may provide subsidies for the implementation of new aerobic physical exercise programs for patients with CRD, to help improve their well-being and QoL.

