### Data analysis

3.3

The data will be analyzed using the Statistical Package for Social Science (SPSS), version 22.0. Descriptive analysis will be performed for all variables. Data will be expressed as mean ± standard deviation or median (interquartile range), where appropriate. The distribution of the sample will be tested with the Shapiro–Wilk test. For the comparison of the initial and final values between groups, the unpaired Student *t* test for parametric distributions and the Mann–Whitney test for nonparametric distributions will be applied. Statistical significance will be considered at the *P* < .05 (or 5%) level.

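### The outcome sections name no patient variable, and a single unranked 5% threshold lets success be claimed on any HRV index, phase or KDQOL-SF dimension

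*Protocol article*

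**What the plan says.** Section 3.1 of the protocol article, headed Primary outcomes, states: "Recruitment began in November 2017 and is underway. A total of 40 patients should be evaluated and submitted to protocol intervention by the end" of the study. Section 3.2, headed Secondary outcomes, opens with "The protocol may provide subsidies for the implementation of new aerobic physical exercise programs for patients with CRD" and adds only that this should help well-being and quality of life.

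The nearest thing to an endpoint statement is the general objective in the Introduction: "to evaluate the effects of aerobic training during hemodialysis on autonomic heart rate modulation and quality of life in patients with CRD". The abstract's objective names autonomic modulation alone. Neither gives an index, a recording phase or a time point.

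The candidate measurements are described elsewhere:
- Section 2.6 on HRV: "The HRV analysis will be performed in time and frequency domain and nonlinear methods". No index is singled out.
- Section 2.7 on recording: "This protocol will be done in 3 phases", namely rest (T1), exercise (T2) and recovery (T3), with the same assessment repeated after 3 months.
- Section 2.7 on the KDQOL-SF: "It is a self-enforcing questionnaire of 80 items divided into 19 dimensions".

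Section 3.3 plans the test as "For the comparison of the initial and final values between groups, the unpaired Student *t* test for parametric distributions", with Mann–Whitney as the alternative. Its decision rule is one sentence: "Statistical significance will be considered at the *P* < .05 (or 5%) level". It gives no order of importance among variables.

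**The concern.** A primary outcome tells the reader in advance which single result answers the trial's question. Here the heading is present but its content is a recruitment report, and the secondary heading holds an aspiration. This is more than detail deferred to a fuller document: the article opens both sections and fills them with something else.

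With no designated result, a change in any HRV domain, in any of three physiologically different phases, or in any quality-of-life dimension could be reported as the trial's positive finding. The target of 40 patients is tied to no variable either. Recruitment has started, so the choice needs to be fixed before final data can influence it.

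**Working it through.** **1. Is an endpoint fixed anywhere?** Setting the sections side by side:

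| Place | Variable | Index | Phase | Time point |
|---|---|---|---|---|
| Abstract, objective | autonomic modulation | none | none | none |
| Introduction, general objective | autonomic modulation and quality of life | none | none | none |
| Sections 2.6 and 2.7 | HRV | three families of methods | T1, T2, T3 | start and 3 months |
| Section 3.1 | none | none | none | none |
| Section 3.2 | none | none | none | none |

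The domain and the two time points can be pieced together. The index and the phase cannot, and nothing is labelled primary.

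**2. Figures in the plan.** The article states no overall error rate, so there is none to reproduce. The target of 40 comes without inputs and can be neither reproduced nor refuted.

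**3. Inputs for the size.**
- Level per test: 0.05 (section 3.3).
- Number of KDQOL-SF scores: 19 (section 2.7). This is the only family that can be counted from the text.
- Number of HRV indices: not given.
- Correlation between tests: not given, so assumed over a range.

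**4. Valid 5% tests, no true change, 19 tests.**
- Expected false positives: 19 × 0.05 = 0.95.
- Chance of at least one under independence: 1 − 0.95^19 = 0.623, or 62%. Fourteen independent tests are enough to pass one half: 1 − 0.95^14 = 0.512.
- With a common correlation between two-sided z tests (simulation, 200,000 draws):

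| Assumed correlation | 19 tests | 30 tests | 40 tests |
|---|---|---|---|
| 0 (formula) | 62.3% | 78.5% | 87.1% |
| 0.3 | 52.6% | 66.2% | 74.5% |
| 0.5 | 40.7% | 50.7% | 57.3% |
| 0.7 | 28.2% | 33.9% | 37.5% |

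The 30 and 40 columns only illustrate what adding HRV tests could do; the document supports neither count.

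**5. The test as now written.** The trial has one group, so initial and final values come from the same patients. With within-patient correlation r, the variance of the mean difference is (1 − r) times what an unpaired test assumes. Its true level is therefore about 2 × [1 − Φ(1.96/√(1 − r))].

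| Assumed r | True level per test | At least one in 19 (tests otherwise independent) |
|---|---|---|
| 0.2 | 2.8% | 42% |
| 0.3 | 1.9% | 31% |
| 0.5 | 0.56% (simulated at n = 40: 0.67%) | 10% |

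**6. With one designated endpoint and a valid paired test**, the false-positive chance for the trial's main claim is 5%.

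**The case against.** The strongest reply is that section 3.3 does not list the variables to be tested. It promises description of all variables, and the first specific objective is only to describe the HRV indexes. A reader might infer that dozens of scores will each be tested, but the text does not say so. It gives no number of HRV indices, and it defines T1 to T3 as recording phases without saying that each is tested separately. Even 19 before-and-after quality-of-life comparisons are an inference: the explicit start and 3-month schedule concerns HRV, the abstract places the KDQOL-SF at the initial assessment, and Figure 1 is not shown. This stands, and it is why the figures above are conditional.

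A reader might also conclude that a chance positive is more likely than not. The documents do not support that. Scores from one questionnaire, or indices from one RR recording, are likely to be correlated, and for the 19 countable dimensions the figure is already below one half at correlation 0.5. The unpaired test as written lowers it further when r is positive. That is no safeguard, however. It is a separate error, and correcting it to a paired test restores the 5% level and with it the multiplicity.

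A reader might further see the HRV target as shifting, since it is described as during exercise in the objectives and after exercise under expected benefits. That is mostly loose wording: sections 2.6 and 2.7 agree on collection at the start and after 3 months. Geometric HRV measures appear only as background in the Introduction and should not be counted among the planned analyses.

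Finally, index lists and multiplicity adjustments are often left to an analysis plan. That is fair for the adjustment method. It does not excuse outcome headings whose content is not an outcome.

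**Conclusion.** The point holds for the outcome definition, and that part needs no assumption: sections 3.1 and 3.2 name no patient variable, and nothing else in the article fixes one HRV index, phase and time point as primary. Combined with a single unranked 5% threshold, this leaves the trial free to claim success on any of several candidates.

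The size is conditional. If the 19 KDQOL-SF dimensions alone were each compared by a valid 5% test with no true change, the chance of at least one false positive would be 62% under independence, about 41% at correlation 0.5 and about 28% at 0.7. The correlations are assumed. Even 28% is more than five times the nominal 5% (28.2/5 = 5.6). Any HRV tests would add to these figures by an amount the document does not allow one to compute.

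**What to change.** Rewrite section 3.1 as one endpoint: one HRV index chosen by the investigators, from one named phase (for example the T1 resting stage), as within-patient change from the start to 3 months, tested with a paired method, two-sided at 5%. Rewrite section 3.2 as a short named list that includes one KDQOL-SF score. Label all other indices, phases and dimensions exploratory, reported as estimates with confidence intervals. Settle this before any final recordings are analysed.

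The cost is wording only; no measurement or visit changes. The small downside is that isolated results below 5% on other indices can no longer be presented as confirmatory.
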